### Data processing and data quality

All data of the CP sample required for the study will be entered using a standardized electronic Case Report Form on a dedicated database, with a secure interface reaching all conditions for maintaining the confidentiality and privacy of data. The database will be programmed to assist for accurate data entry (data dictionary, fields controls). Additional data validation will be done. At centre level, a random sample of 10% of cases will be audited against entered data by a staff not involved in the initial data entry. The acceptable error rate will be set at < 1% of the items. Further validations will be performed after exporting the data into a statistical package: extent and pattern of missing data, heterogeneity between centres, and potential for bias due to non-response. We will assess whether non-response is related to the severity of impairments, socioeconomic status of the individual, and whether any such association can explain differences in response rates between centres.

All data of the general population sample will be collected on line using appropriate software. After the targeted sample sizes have been reached, the survey data will be checked for sufficient quality according to various criteria, including interview duration, response variance of the matrices, and validity of the answers. Participants with an interview duration of less than half of the average time for completion will be referred to as “speeders”. The variances of the answers will be calculated for all matrices in the questionnaire (except for filter questions). Participants who will have an overall standard deviation below 0.5 will be assumed to show low response variance and referred to as “straight-liners”. Another criterion for invalid data will be “fake” responses to open questions. For this purpose, all open responses will be checked. If an answer does not correspond with the respective question or contain only a random sequence of letters, data of the respondent will be excluded.

### Power calculations

Considering that the cross sectional samples will comprise of 300 to 350 young adults with CP and a ratio of at least 1 in 10 for the CP sample as compared to that of the general population (Table 1), we will be able to document with over 80% power (type I error 0.05, bilateral) differences in participation between young adults with CP and those from the general population expressed as odds ratios (OR) (OR > 1 means that young people with CP participate less than the general population) as high as OR = 1.5 for activities achieved by 50% of the young adults with CP to 1.9 for less frequent activities (10% of the population with CP involved). Potentially eligible longitudinal CP sample consists of 416 young adults. Given an expected participation rate of 60%, we expect to enrol 245 persons of the SPARCLE cohort with CP.

### Statistical analyses

Psychometric analysis of the assessments will be applied, with special emphasis on revised, translated and newly developed measures. These analyses will include reliability, convergent and divergent validity and Differential Item Functionning across countries.

The study variables of main interest (participation, QoL, environmental factors) will be studied by domains. They correspond to unobserved or latent variables, manifested by responses to the items in the corresponding questionnaires. Measurement models will be specified and validated. For each domain, one model will be defined comprising a ‘measurement part’ that defines the latent constructs (sets of observed variables in accordance with Item Response Theory (IRT)), and a ‘structural part’ that hypothesises the links between these constructs in accordance with Structural Equation Modelling (SEM) methods. The structural part will specify the hypothesised links between the variables, both latent and observed. We will hypothesise that this domain in adulthood may be directly affected by the concurrent factors we will identify.

For the longitudinal analyses, we will hypothesise that each factor earlier in life could directly or indirectly (via its influence on mediating variables) affect a given domain in adulthood. The analysis will consider the same dimensions at the different periods as different variables, because of differences in questionnaires. The more parsimonious models will be taken in account. Sensitivity analysis will be performed to assess the possible effect of technical choices in parameters of SEM. Missing values will be imputed from predictors of drop-out using multiple imputation methods.

A conceptual overview on the association of QoL and well-being measures with the participation measure will be carried out. Therefore, we will explore a) the continuum of QoL and well-being measures, b) the conceptual inclusion of participation facets in QoL and well-being measures, and c) the impact of selective psychological comorbidity on participation. Using data collected in young adults with CP, we will investigate the comparability of the two WHOQOL-BREF versions for disabled persons vs. healthy persons [72], applying randomized assignment of different rating scale formats within the population based control group and applying item-response theory driven scaling and item parameter analysis.

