**Methods:**

The SPARCLE3 study has a combined longitudinal and cross-sectional design. Young adults with CP aged 22 to 27 years in 6 European regions previously enrolled in the SPARCLE cohort or newly recruited will be invited to self-complete a comprehensive set of questionnaires exploring participation (daily life and discretionary activities), health-related quality of life, body function, personal factors (health, personal resources), and contextual factors (availability of needed environmental items, family environment, services provision) during home visits supervised by trained researchers. Proxy-reports or adapted questionnaires will be used for those with the most severe impairments. The recruitment of a large group from the general population (online survey) will enable to identify life areas where the discrepancies between young people with CP and their able-bodied peers are the most significant.

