### Data collection procedures

All participants in the SPARCLE cohort (*Longitudinal CP sample*) previously gave their permission to be contacted again for a further study. Prior to any investigation, the vital status of the participants will be checked. After a phone contact, written information about the objectives of the study and the activities for participants will be sent. There will be at least 7 days between arranging the appointment for a home visit and completion of questionnaires after the final consent is obtained. Pretesting the questionnaires, we estimated that the participation in the study will take between 2 to 6 hours, which may spread over 1 or 2 days according to participant’s health. Persons who moved out of the catchment area will be contacted and possibly included (home visit if feasible, otherwise telephone interview). For new participants (*Supplementary CP sample*), a health professional such as a neurologist or a general practitioner will approach the person or their legal representative. Apart from this, similar procedures for home visits will be applied.

Information will be collected by trained researchers to ensure consistency across regions. Questionnaires will be administered in a logical flow and fixed order, and self-completed whenever possible. For persons with motor or communication difficulties or unclear speech, the research assistant will explain, answer queries, and assist if needed. Picture versions of some instruments or answering scales will be used at the research assistant’s discretion. In case self-assessment will not be possible even with help, the questionnaires will be filled out by the personal assistant or any individual (including parents) who knows the young adult very well (meaning that they are significantly involved in their daily life). For the general population, information will be collected using computer-mediated communication. The completion duration will be 10 to 20 min.

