Briefly, QoL will be assessed using the WHOQOL-BREF [50, 51]. Because reference data is difficult to obtain for the studied age range, the instrument will be completed by the general population as well. The disability answering scale (disability module [72]) will be used when necessary. A picture version (adapted Talking Mats version [73]) will be used optionally to enable those with the most severe disabilities to self-report, in addition to proxy-reports. Although not developed for the age range of the study participants, KIDSCREEN-10 index [52] will be used in the *Longitudinal CP sample* to allow direct comparisons across time. For participation, several instruments will be used. First, the WHO Disability Assessment Schedule (WHODAS) 2.0 instrument [53] will be filled in by young people with CP as a measure of difficulties in achieving activities in five dimensions, and participation in one. Second, we sought to measure participation as involvement in life situations from the perspective of participants with the frequency of attainment independent from the dimension of activities and functioning. Therefore, an instrument based on the previously validated Questionnaire of Young People’s Participation (QYPP [54];) was developed. Using group discussions, eight young adults with and without CP from northern Germany were asked about their perceptions of participation. In addition, five expert interviews were conducted with parents and professionals to indirectly include young adults with a more severe profile. The interviews were transcribed and analysed using qualitative content analysis. To fully reflect the areas identified (education and work, finances, leisure, social relationships, media, autonomy and mobility), 15 items were developed and added to the eight selected items of the original QYPP. Eleven cognitive interviews were then conducted to pilot the first version of the new instrument. They led to minor adaptations. The final version of QYPP-Young Adults (QYPP-YA) comprises 22 items measuring frequency of participation in selected areas of life. It was translated to the other languages according to international standards, and will be assessed in young people with CP and the general population.

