We also intend to compare the outcomes i.e. QoL, participation, psychological well-being, as well as the determinants (education, work, health and social fields, health care services) with the general population, and therefore selected instruments suitable for the general population. Online surveys, which are widely used for research, represent a potentially quick and affordable method of recruiting study participants from the general population. Of potential concern is the sample representativeness. We will compare overall figures to those obtained from other representative surveys whenever possible. Comparative analyses will help identify in which areas the opportunities for general health, psychological well-being, education, employment, independent living, social relations, and participation are the most afflicted, and determine the impact of environmental factors including access to health care. Comparisons between regions will identify if variations exist in patterns due to different approaches to organize services (notably the health care system) and support. Finally, our study will provide policy-makers, health professionals, and families (parents, siblings) with rigorous data collected in various settings to help overcome the barriers that this population encounters every day.

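### Differential item functioning is named only by country, although Aim 3 compares CP and general-population scores collected with different answer formats, respondents and modes

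*Protocol article*

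**What the plan says.** The psychometric plan in Statistical analyses reads: "These analyses will include reliability, convergent and divergent validity and Differential Item Functionning across countries". Country is the only grouping factor named. The same section says that measurement models will be specified and validated, and that new, revised and translated instruments get special emphasis.

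Data from the CP group are collected in several ways:

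- The Abstract (Methods) places completion "during home visits supervised by trained researchers"; Data collection procedures adds telephone interviews for some who have moved away.
- On the WHOQOL-BREF, the Measurements section says "The disability answering scale (disability module [72]) will be used when necessary".
- Data collection procedures says "Picture versions of some instruments or answering scales will be used at the research assistant’s discretion".
- Where self-report fails even with help, "the questionnaires will be filled out by the personal assistant or any individual (including parents) who knows the young adult very well".

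The comparison group is handled differently: "For the general population, information will be collected using computer-mediated communication". The survey is anonymous and comes from an access panel (Study participants).

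The two groups are then set against each other. The third aim at the end of the Background compares participation frequency and QoL with the general population, and the Discussion repeats it: "We also intend to compare the outcomes i.e. QoL, participation, psychological well-being".

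One further analysis bears on this. The last paragraph of Statistical analyses plans to examine whether the two WHOQOL-BREF versions are comparable, "applying randomized assignment of different rating scale formats within the population based control group", with IRT scaling and item parameter analysis. That sentence opens by locating the investigation in the data from the young adults with CP.

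**The concern.** A score difference between two groups is a difference in the construct only if the items work the same way in both. Here at least three features of measurement change together with CP status: the answer scale (for some), the respondent (for some) and the mode (for nearly all). The item-level check that the article names is by country, which protects between-country comparisons. It does not protect the CP versus general-population contrast, which is Aim 3 and the contrast on which the power statement rests.

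The gap matters most for the QYPP-YA. In Table 2 it is the only participation instrument given to the general population, because the WHODAS 2.0 goes to the CP samples alone. It is a new 22-item adaptation. The whole participation contrast therefore depends on its items behaving alike in the two groups, and the article names no check of that.

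At stake is whether a reported gap reflects the lives of young adults with CP or how they were asked. The error could also run the other way, with a measurement shift hiding a real gap.

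**Working it through.** **1. What differs, and which check is stated.**

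| Feature | CP group | General population | Stated check |
|---|---|---|---|
| WHOQOL-BREF answer scale | standard, or disability scale if needed | formats randomised | version comparability study (IRT) |
| Picture versions | at the assistant's discretion | none described | none stated |
| Respondent | self, assisted self or proxy | self | none stated |
| Mode | supervised home visit, some telephone | anonymous web survey | none stated |
| QYPP-YA items | CP samples | general population | DIF by country |

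**2. The plan's own power figure.** Inputs from Power calculations: 300 to 350 with CP, a ratio of at least 1:10, two-sided 0.05, OR 1.5 at 50% participation in CP and OR 1.9 at 10%. The general-population proportion is odds/(1 + odds), with odds = OR × p/(1 − p). This gives 1.5/2.5 = 0.600 and 0.2111/1.2111 = 0.174.

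Power is Φ[(d − 1.96·SE0)/SE1], with SE0 pooled and SE1 unpooled. For 0.5 versus 0.6 with 300 and 3000, SE0 = √(0.5909 × 0.4091 × (1/300 + 1/3000)) = 0.0298 and SE1 = √(0.25/300 + 0.24/3000) = 0.0302. Power = Φ((0.1 − 0.0584)/0.0302) = Φ(1.378) = 91.6%. For OR 1.9 at 10% the power is 94.6%. With 350 the values are 95.0% and 97.3%. The claim of over 80% holds and is not in dispute.

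**3. How small a score shift could reach significance.** On a standardised mean score, SE = √(1/300 + 1/3000) = 0.0606 SD. The minimum detectable difference at 80% power is (1.960 + 0.842) × 0.0606 = 0.17 SD.

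Now assume no true difference and a shift of δ in a share s of CP respondents. The apparent gap is s·δ. Neither s nor δ is in the document.

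- δ = 0.2 SD, s = 30%: gap 0.06 SD, gap/SE = 0.99, two-sided rejection 16.8%.
- δ = 0.2 SD, s = 60%: gap 0.12 SD, gap/SE = 1.98, rejection 50.9%.
- δ = 0.2 SD, s = 100% (as for a mode effect): gap 0.20 SD, rejection about 91%.

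**4. The same on a participation item.** Assume 50% participate in both groups and an artefact OR of 1.5 in a share of CP respondents. An affected respondent's probability becomes 0.4. With 30% affected, the observed CP proportion is 0.7 × 0.5 + 0.3 × 0.4 = 0.47, and the apparent OR is 0.53/0.47 = 1.13. For shares of 20%, 30%, 50% and 100% the apparent OR is 1.08, 1.13, 1.22 and 1.50. The chance of a significant lower result in CP is about 10%, 17%, 38% and 91%.

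**5. What the WHOQOL-BREF version study can identify.** Randomisation within the general population identifies the format effect there. In CP the scale is given when needed, so a comparison of formats within CP mixes the format with whatever created the need. The article does not say that the result will adjust or restrict the Aim 3 comparison.

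**6. What DIF by group can identify.** It flags items that behave differently relative to the others. A shift common to all items, as mode might produce, looks exactly like a true difference and stays invisible.

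**The case against.** The strongest reply has five parts.

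- **Answer format is not ignored.** A reader might infer that it goes wholly unchecked. That is wrong for the WHOQOL-BREF, where a randomised-format IRT study is planned. This stands. What remains are its limits: the reliance on need-assigned CP data, the uncovered picture versions, and the missing link to Aim 3.
- **Proxies belong to Aim 4.** The third aim concerns what young adults with CP themselves report, while adapted materials and proxies are named under the fourth. A reader might infer that proxy scores will be pooled into the Aim 3 contrast; the document does not say so. This stands, and the fix only makes that reading explicit.
- **The DIF list is open.** It is introduced as what the analyses include, and a condensed article may leave further factors to a fuller plan. This stands in part. The article does choose one grouping factor to name, and it is not the one on which its between-group aim depends.
- **The figures rest on assumptions.** No shift size, affected share or direction appears in the document, and the calculation takes all shifts to run one way. This stands; the figures show sensitivity and do not predict bias.
- **DIF testing cannot repair mode.** This stands too, so mode is treated below as a limitation to declare.

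That need-assigned format tracks severity is also an inference. The text says only that the scale is used when necessary.

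**Conclusion.** The point holds in a limited form and is worth acting on before analysis. The named item-level check is by country, while Aim 3 needs comparability between CP and general population on the QYPP-YA and WHOQOL-BREF. The planned version study covers part of the answer-format question for one instrument and nothing else in the table.

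It is tempting to conclude that measurement artefacts will be reported as QoL or participation gaps. The document supports only that they may be, because neither size nor direction can be fixed from it. Under the assumed 0.2 SD shift in 30% to 60% of CP respondents, the false-positive rate would be about 17% to 51% at 300 versus 3000. This assumes no true difference, equal variances and shifts in one direction. If self-report is kept for Aim 3, the proxy part of that share drops out and the figure falls.

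The sample size and power statement are unaffected.

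**What to change.** 1. Extend DIF or invariance testing of the QYPP-YA and WHOQOL-BREF to CP versus general population and, within CP, to self versus proxy (descriptive where numbers are small). Free the items that are not invariant.
2. Estimate the WHOQOL-BREF format effect from the randomised general-population arms, not from CP formats assigned by need.
3. State that the Aim 3 contrast uses self-reports, as its wording implies. Add a format-matched sensitivity comparison: CP participants on the standard scale against the standard-scale general-population arm. Show proxy and alternative-format results separately under Aim 4.
4. State the home-visit versus online difference as a limitation that DIF testing cannot resolve.

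**Cost.** This is analysis wording, plus a field for format and respondent per instrument if the case report form does not already hold one. The matched comparison is smaller. If a fraction f of both groups remains (f is not in the document), the minimum detectable difference becomes 0.170/√f: 0.20 SD at f = 0.7, 0.24 SD at 0.5 and 0.27 SD at 0.4. The matched CP participants are also likely to be a less severely affected subgroup, and the result should be labelled so. Format effects estimated in the general population may not carry over fully to CP, which is a reason to show the matched comparison beside any adjusted one.

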## Discussion

This project is intended to document the impact of the physical, social, attitudinal, and health care services environment on participation and QoL in young adults with CP. We hypothesise that restricted participation of disabled people could be attenuated or even removed by changes in their environment with, for example, adaptations to their physical surroundings, the provision of equipment and an assumption of capacity by people in their community. The longitudinal perspective in addition with comparisons with the general population will improve our understanding on which factors of the environment have the higher impact on a beaming young adulthood.

We first designed a longitudinal approach with three time points allowing for intra-individual comparisons across time and the study of the shape of trajectories of interest. There are inherent conceptual and methodological issues in the assessment of change over time. One key issue was to determine the appropriate time point taking into account practical issues related to length of interval between previous and current waves (update of contacts, occurrence of migrations out of the area, attrition rate). In the SPARCLE3 study, we intended to explore the transition period of adolescence to young adulthood. However, we must expect a wide variation in developmental trajectories, also depending on the availability of resources and environmental, both physical and social, factors. Even if the concepts explored from childhood are similar, both the areas of interest and the representation of these concepts may change in the individual developmental course, which requires adaptation of questionnaires used in childhood or adolescence, or use of measurements developed for adults.

We also intend to compare the outcomes i.e. QoL, participation, psychological well-being, as well as the determinants (education, work, health and social fields, health care services) with the general population, and therefore selected instruments suitable for the general population. Online surveys, which are widely used for research, represent a potentially quick and affordable method of recruiting study participants from the general population. Of potential concern is the sample representativeness. We will compare overall figures to those obtained from other representative surveys whenever possible. Comparative analyses will help identify in which areas the opportunities for general health, psychological well-being, education, employment, independent living, social relations, and participation are the most afflicted, and determine the impact of environmental factors including access to health care. Comparisons between regions will identify if variations exist in patterns due to different approaches to organize services (notably the health care system) and support. Finally, our study will provide policy-makers, health professionals, and families (parents, siblings) with rigorous data collected in various settings to help overcome the barriers that this population encounters every day.

